#### Sample size

3.4.2

Previous risk communication intervention studies were utilized to estimate the sample size. In our previous survey (46), we observed a baseline proportion of healthy lifestyle adherence at approximately 30% among participants with familiar sample characteristics. For the intervention groups, we anticipate a relative increase of at least 50% (47), with an expected difference of 25% between the gain- and loss-framed groups (39). This corresponds to an estimated effect size (W) for Chi-square of 0.20 (48), aligning closely with recommendations from prior studies (38). To achieve a power of 80%, an alpha error rate of 0.05, a standard deviation of 5%, and an estimated effect size (W) of 0.20, a total of 198 participants will be required for our primary outcome, which measures a healthier lifestyle encompassing physical activity, diet, and prevention medication at 3 months. These participants will be evenly distributed into three groups: gain-framed, loss-framed, and no-frame message interventions. However, considering the dropout rate of 20%, a sample size of 240 participants will be required.

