#### Data analysis

3.8.1

Descriptive statistical analysis will be conducted for all measurements. The distributions of categorical baseline variables will be compared using χ^2^ test among the three intervention groups. The difference in continuous variables will be analyzed using either one-way analysis of variance (ANOVA) or a non-parametric rank-sum test. The differential changes in the primary (i.e., healthy behaviors) and secondary (i.e., risk perception) outcomes at T1 and T2, relative to T0, across the three groups will be assessed using generalized estimating equations (GEE) models. GEE methods were applied to estimate model parameters using a binomial distribution for the variance function, a logit link function, and accounting for clustering via an assumed exchangeable working correlation structure (65). The outcomes will be used as dependent variables (one for each model) and, as independent variables, the intervention arms (no-framed, gain-framed, loss-framed message), the factors time (T0, T1, T2), the covariates (risk perception categories) and their corresponding interaction term. The other potential confounders (i.e., variables with baseline imbalances, study sites) will be added as independent variables to adjust GEE model. An exchangeable working correlation structure will be assumed in order to assess the association between factors and outcomes. The statistical significance of each parameter in the model will be analyzed using a Wald test. To account for the potential occurrence of type 1 errors, a Bonferroni correction will be implemented for all GEE models, with a *p*-value threshold of less than 0.003 indicating statistically significant differences (66). The final model’s results will be presented as estimated odds ratio (*OR*) and 95% confidence interval (*CI*) for each significant prognostic variable. We will also conduct the sensitivity analysis to assess the non-response mechanism (67) and an attrition analysis (68) to identify the differential dropout rates and dropout by group interaction on sociodemographic and pretest variables that may pose a threat the equity of the findings (69). Subgroup analysis was performed for cases that did not pass the manipulation check. The principle of “intention to treat (ITT)” will be applied in conducting all primary and secondary outcome analyses. Moreover, the patterns of missingness would be recorded across variables and time points to provide insight into non-random missingness. Statistical significance will be determined by results with *p* < 0.05 in two-sided tests. The analysis will be carried out using SPSS software for MAC (version 26.0) and R software (version 4.3.1).

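### The trial is sized on gain-framed versus loss-framed at 3 months, but the analysis tests model parameters one by one and names no deciding contrast, so the sized comparison need not be tested

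*Protocol article*

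**What the plan says.** **Protocol article, 3.4.2 Sample size.** The section starts from a baseline: "we observed a baseline proportion of healthy lifestyle adherence at approximately 30% among participants". It continues: "For the intervention groups, we anticipate a relative increase of at least 50" per cent, "with an expected difference of 25% between the gain- and loss-framed groups". This is converted to a chi-square effect size of 0.20. With 80% power and alpha 0.05 it gives 198 participants in three equal groups, raised to 240 for dropout. The outcome is one "which measures a healthier lifestyle encompassing physical activity, diet, and prevention medication at 3 months".

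**Protocol article, 3.8.1 Data analysis.** Changes in the "outcomes at T1 and T2, relative to T0, across the three groups will be assessed using generalized estimating equations (GEE) models". The independent variables are arm (no-framed, gain-framed, loss-framed), time (T0, T1, T2), risk-perception category and their interaction. The testing rule is: "The statistical significance of each parameter in the model will be analyzed using a Wald test". Odds ratios are to be reported for variables found significant. A Bonferroni threshold of p < 0.003 is set for all GEE models, and a later sentence sets p < 0.05, two-sided.

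**Elsewhere.** Section 3.6.1 labels the no-framed arm as control. Table 1 schedules the behaviour measures at T0, T1 and T2, but the 10-year and lifetime CVD risk calculations only at T0 and T2. No section names a reference level, a primary contrast, a joint test of the arm-by-time terms, or a primary analysis time point.

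**The concern.** The sample size section names one between-arm difference and one time point. The analysis section sets a rule that tests whatever coefficients the software happens to print. Those coefficients depend on coding that the article does not fix. Under the most natural coding, the comparison named in the sizing is not among them.

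The candidate results can also disagree. The frames may differ from each other while neither differs clearly from no-frame. Both may beat no-frame equally. An effect at T1 may have gone by T2. Without a named deciding contrast, the effect the trial was sized for could go untested, or the arm pair and time point could be settled after the results are known.

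**Working it through.** **1. Reproduce 198.** Inputs from 3.4.2: W = 0.20, alpha 0.05, power 80%. The degrees of freedom are not stated. Chi-square power uses the noncentrality λ = N × W², so N = λ / 0.04.

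- 1 df: λ = 7.85, N = 196.2, so 197 (198 as a multiple of three).
- 2 df: λ = 9.63, N = 240.9, so 241. At N = 198 the power is 71%.
- 4 df: λ = 11.94, N = 298.4, so 299.

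Of these, only 1 df, a single two-group comparison, reproduces 198.

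**2. What the parameter-wise rule tests.** Take no-framed and T0 as reference levels. The arm-by-time coefficients are gain vs none at T1 and T2 (G1, G2) and loss vs none at T1 and T2 (L1, L2). Gain vs loss at T2 is G2 − L2, with variance Var(G2) + Var(L2) − 2Cov(G2, L2). It is a combination of two coefficients and gets no Wald test of its own. With gain or loss as reference it would be a coefficient, but another arm pair would drop out: any reference level yields two of the three pairs.

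If the interaction is arm × time × risk perception, the model has 3 × 3 × 3 = 27 parameters before site and confounder terms. Under reference coding, G2 and L2 then apply only to the reference perception category.

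**3. Does the choice of contrast change the answer?** Simulation with 240 × 0.8 = 192 completers (64 per arm), baseline 30%, within-person latent correlation 0.5, and Wald tests of the change in log-odds from T0 to T2. The T2 rates and the correlation are assumptions.

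| T2 rates: none / gain / loss | Gain vs loss | Gain vs none | Loss vs none |
|---|---|---|---|
| 45 / 57.5 / 32.5% | 64–66% | 20–22% | 24% |
| 30 / 45 / 45% | about 5% (no difference) | 31% | 31% |
| 30 / 70 / 45% | 65% | 96% | 31% |
| 45 / 70 / 45% | 65% | 66% | about 5% (no difference) |

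Entries are rejection rates at 0.05. In the first row, 27% of runs have gain vs loss significant while neither frame-vs-none test is. In the third row at 0.003, gain vs none has 77% and gain vs loss 26%.

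**4. Number of candidate results.** A behaviour outcome has 3 arm pairs × 2 times = 6 contrasts. CVD risk is not calculated at T1, so it has 3. With no true effect, the chance of at least one false positive among the six is 18 to 22% at 0.05 (T1/T2 correlation 0.8 to 0.3), and 1.4 to 1.7% at 0.003.

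**5. Power if gain vs loss decides.** 198 / 3 = 66 per arm, so 132 in the two arms. With W = 0.20 and 1 df, power is 63% at 0.05 and 25% at 0.003. A plain comparison of 45% with 70% at 3 months has 84% and 47%; 45% with 56.25% (25% read as relative) has 25% and 5%.

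**The case against.** **The reference level is unstated, so nothing excludes gain vs loss.** This stands. A reader might infer that the plan rules the comparison out. It does not: with another reference level it would be a coefficient, and under any coding it can be computed from the same fit. What remains is that the stated rule does not secure it.

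**This is detail for an analysis plan.** Only partly. Reference coding and contrast statements often sit there. But section 3.8.1 states a testing rule, and that rule does not follow from the sizing in 3.4.2.

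**The sizing does not rest on gain vs loss alone.** This stands as a caveat. The 50% relative increase is also an input. A 25-point difference of 45% vs 70% gives W = 0.25 / (2 × √(0.575 × 0.425)) = 0.25, not 0.20. The three rates 30%, 45% and 56.25% give a three-arm W of 0.22. Even so, gain vs loss is the only between-arm difference named, and 198 fits only 1 df.

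**False positives are already controlled.** A reader might infer a family-wise error of about 21%. That holds only under the p < 0.05 sentence. Under the article's own 0.003 threshold for GEE models it is about 1.5%. That threshold limits error but does not say which result decides.

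**The large power loss comes from rates the plan does not assume.** This stands. The 20 to 24% powers put the loss-framed arm at 32.5%, below control at 45%, whereas the sizing expects at least 30% × 1.5 = 45% in the intervention groups. In the third row, which fits that expectation, gain vs control is the more powerful test.

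**It is a pilot.** The article says so, but it also sizes the trial for 80% power and aims to identify the optimal message.

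**Conclusion.** The concern holds as a mismatch between sizing and testing. The article names gain vs loss at 3 months when it sets the sample size, then prescribes parameter-wise Wald tests that need not include that comparison and that give T1 and T2 equal standing. If the interaction is three-way, they may also describe only one perception category. The deciding result is therefore open to coding, arm pair and time point.

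The size of the harm is conditional. Loss of power is large if control lies between the two frames, and absent if both frames exceed control as anticipated. Inflation of false positives applies only at 0.05. The documents do not support a claim that the trial must miss its effect or that its error rate is four times nominal. The 1-df reading is inferred, because only it reproduces 198. The simulated powers rest on assumed rates and an assumed correlation. This should be fixed, but it is not fatal to the design.

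**What to change.** In section 3.8.1, for each primary behaviour outcome, replace the parameter-wise tests with one of two rules:

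- **Joint test first.** A 2-df Wald test of arm-by-T2 (change from T0, averaged over risk-perception categories). If it is significant, follow with the three pairwise T2 contrasts, gain vs loss included. With three arms this needs no further correction within one endpoint.
- **Single contrast.** Gain vs loss, T0 to T2, averaged over risk-perception categories, as the one primary linear contrast. This matches section 3.4.2.

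Label all T1 contrasts secondary under either rule. Neither rule covers multiplicity across the several primary components, which still needs its own rule, and the 0.003 and 0.05 thresholds must be reconciled.

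**Cost.** A few sentences and one contrast or joint-test statement in the software, written before the group codes are opened. A T1-only result can no longer be called primary. Under the single-contrast rule, neither can a frame-vs-none result. Naming the contrast does not supply its power: at W = 0.20 and alpha 0.05, 198 participants give the joint test 71% and gain vs loss 63%, so the power statement should be restated for the rule chosen.

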#### Secondary outcomes

3.7.2

Secondary outcomes include CVD risk perception, efficacy belief, CVD related knowledge, major adverse cardiovascular events (MACE), the emotional response, physical indicators (Blood pressure, blood glucose, waist circumference and BMI) and other lifestyle related risk factors [smoking, drinking status, and subjective health status (60)].

CVD risk perception, efficacy belief and CVD related knowledge will be evaluated using the Chinese version of Attitude and Beliefs about Cardiovascular Disease Risk Questionnaire (ABCD-C) (49), which comprises 26 items across four dimensions. Efficacy belief will be assessed using the item 19, 20, 22, and 24, following the recommendation by Rimal and Juon (61). This scale has demonstrated good validity and reliability in both its original and Chinese versions, as evidenced by Cronbach’s α values ranging from 0.70 to 0.94. The emotional response will be assessed using two items on a 10-point scale (1–10; with a total range of 2–20), which have been adopted from the existing literature (62). An example of such item is “How concerned are you by reading this information?.” MACEs are defined as the composite endpoints of cardiovascular death, spontaneous myocardial infraction, and target vessel revascularization at 3 months follow up (63). The smoking and drinking status, as well as physical indicators, were extracted from the follow-up records of participants by GPs.

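### The 0.003 Bonferroni threshold covers about 16 to 17 tests, too few for the parameter-wise testing of all GEE models to which it is applied

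*Protocol article*

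**What the plan says.** Section 3.8.1 (Data analysis) of the protocol article sets four things together.

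- **Models.** Primary and secondary outcomes are analysed by GEE: "The outcomes will be used as dependent variables (one for each model"). Predictors are arm (three levels), time (T0, T1, T2), risk perception category (three levels), an interaction whose order is not given, and confounders.
- **Unit of testing.** "The statistical significance of each parameter in the model will be analyzed using a Wald test".
- **Threshold.** "a Bonferroni correction will be implemented for all GEE models, with a *p*-value threshold of less than 0.003" marks significance. No divisor or list of tests is given.
- **A second rule.** The same paragraph later says: "Statistical significance will be determined by results with" p below 0.05, two-sided. It does not say which tests this governs.

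Section 3.7.1 lists the primary outcomes: three behaviours (physical activity, diet, preventive medication) and CVD absolute risk, both 10-year and lifetime. Section 3.7.2 adds a long list: "Secondary outcomes include CVD risk perception, efficacy belief, CVD related knowledge, major adverse cardiovascular events (MACE), the emotional response, physical indicators" and others. Section 3.4.2 sizes the trial at the unadjusted level: "To achieve a power of 80%, an alpha error rate of 0.05".

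**The concern.** A Bonferroni threshold protects only the number of tests it was divided by. Here the protocol names its unit of testing (each parameter), its scope (all GEE models) and a number (0.003), and the three do not fit together. A single parameter below 0.003, in any of the models, could be reported as a multiplicity-protected finding when the protection is weaker than claimed. The exposure is greatest for the question of which frame suits which risk perception group, because the terms that answer it add the most parameters.

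There is also a cost in the other direction. Putting primary and secondary outcomes under one correction makes the primary outcomes pay for the secondary ones, at a threshold the sample size did not allow for.

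**Working it through.** **1. The plan's own figure.** 0.05/0.003 = 16.7. Sixteen tests give a bound of 16 × 0.003 = 4.8%. Seventeen give 5.1%, or 1 − 0.997^17 = 4.98% if independent. The divisor is not stated; rounded to three decimals, 0.003 fits 15 to 19 tests.

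**2. Outcomes (sections 3.7.1, 3.7.2 and Table 1).** There are 5 primary outcomes. Secondary outcomes number 12 if blood pressure counts as one: risk perception, efficacy belief, knowledge, MACE, emotional response, blood pressure, glucose, waist, BMI, smoking, drinking and subjective health. That makes 17, and 0.05/17 = 0.0029, so 0.003 looks like one test per outcome. This is an inference. MACE and emotional response are each measured once, which leaves 15 repeated-measures outcomes. Two of these (10-year and lifetime risk) are calculated at T0 and T2 only.

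**3. Randomised-effect parameters on change, per model.**

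- Arm × time: 2 × 2 = 4 with three visits; 2 × 1 = 2 with T0 and T2 only.
- Arm × time × perception category, if fitted: 2 × 2 × 2 = 8, or 2 × 1 × 2 = 4.

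Time, category, site and confounder parameters are left out, although the text read literally tests them too.

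**4. Family-wise error at 0.003 per test.** Bound = 0.003m; independent = 1 − 0.997^m.

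| Family | Tests m | Bound | If independent | 0.05/m |
|---|---|---|---|---|
| One joint test per repeated-measures outcome | 15 | 4.5% | 4.4% | 0.0033 |
| One joint test per listed outcome | 17 | 5.1% | 5.0% | 0.0029 |
| Arm × time, primary outcomes: 3×4 + 2×2 | 16 | 4.8% | 4.7% | 0.0031 |
| Arm × time, 15 outcomes: 13×4 + 2×2 | 56 | 16.8% | 15.5% | 0.0009 |
| Arm × time plus three-way, primary: 3×12 + 2×6 | 48 | 14.4% | 13.4% | 0.0010 |

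**5. Allowing for correlation (simulated Wald statistics, linear approximation, equal cells, assumed correlation of 0.5 between visits).**

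- Arm × time over 15 outcomes: 15.4%, 14.1% and 10.4% at between-outcome correlations of 0, 0.3 and 0.6. This run gave every outcome three visits (60 parameters rather than 56), so it slightly overstates.
- Arm × time plus three-way, five primary outcomes: 11.3 to 11.5% at correlation 0, 9.4 to 10.0% at 0.5, and 7.7% at 0.8.

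**6. Power at the two thresholds.** With W = 0.20 and a 1-df chi-square, the noncentrality is N × 0.04. Power of 80% at 0.05 needs N = 197, which reproduces the plan's 198 (three groups of 66).

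- N = 198: √7.92 = 2.814. At 0.05, Φ(2.814 − 1.960) = 80%. At 0.003, Φ(2.814 − 2.968) = 44%.
- N = 240: √9.6 = 3.098. At 0.003, Φ(3.098 − 2.968) = 55%.

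**The case against.** The strongest reply is that the protocol never defines the family, so an excess cannot be asserted without choosing one, and ordinary families exist for which 0.003 is right. One joint test per outcome (15 to 17 tests) holds about 5%. So do the 16 arm-by-time parameters of the primary outcomes, which match the section's stated interest in differential change across arms. The wording about parameters may also be loose, since results are to be reported by prognostic variable. The family and testing order could sit in an unseen SAP, and the study calls itself a pilot.

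Part of this stands. The size of the excess cannot be fixed from the document, and a missing testing order alone would be no finding. But neither of the families that fit is the one described. A joint test per outcome is not a test of each parameter. The 16-test family covers only the primary outcomes, although the correction is stated for all GEE models, and it omits the framing-by-perception question in the objectives. A SAP would have to change one of the protocol's own statements. As for the pilot label, the plan itself invokes type 1 error control.

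A reader might go further and count a three-way interaction in every model for all outcomes, which gives about 180 tests and a family-wise error near 26%. The documents do not support that as a headline. The interaction order is not given, and the figure treats secondary outcomes as confirmatory.

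**Conclusion.** The concern holds in a limited form. The fixed threshold of 0.003 does not match the parameter-wise testing of all GEE models to which it is applied. Family-wise error is about 10 to 15% when only arm-by-time parameters are counted over 15 repeated-measures outcomes. It is about 8 to 12% for the five primary outcomes alone if three-way terms are fitted. These ranges rest on the outcome count above, equal cells, and the assumed correlations.

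Two further statements do not agree with 0.003: the unadjusted 0.05 rule in the same section, and the sample size calculated at 0.05. It should not be inferred that every reading of the plan exceeds 5%; narrower families do not. Nor should it be inferred that the threshold must be lowered. What is needed is a named family and a threshold that follows from it.

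**What to change.** In section 3.8.1:

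- Replace parameter-wise testing with one joint Wald test per primary outcome and question: arm × time, and arm × time × perception category.
- Apply Holm or Bonferroni at an overall 0.05 to that named primary family and derive the threshold from it, in place of 0.003. Five outcomes × two questions = 10 tests gives 0.05/10 = 0.005.
- Report secondary outcomes as exploratory.
- State which tests, if any, the p < 0.05 rule governs.

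The cost is wording, plus a loss of claims: secondary and single-parameter results can no longer be declared confirmatory. The change does not restore the planned power. At 0.005 the same 1-df test has Φ(2.814 − 2.807) = 50% power with 198 participants and Φ(3.098 − 2.807) = 61% with 240. The sample size section should therefore say which alpha it is meant to support.

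### Two significance thresholds (0.003 and 0.05) are left unreconciled, and the trial is sized only at 0.05; if 0.003 governs the primary tests, the stated 80% power falls to roughly 32–44%

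*Protocol article*

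**What the plan says.** The statements that bear on this point are in two sections of the protocol article.

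- **3.8.1 Data analysis.** GEE models assess the primary and the secondary outcomes across the three arms and three time points, with risk perception category and the interactions in the model. A Bonferroni correction applies to all of these models, with a "threshold of less than 0.003 indicating statistically significant differences".
- **3.8.1, later in the same paragraph.** "Statistical significance will be determined by results with" p < 0.05, two-sided. No particular tests are named.
- **3.8.1, reporting.** Odds ratios and 95% confidence intervals are to be presented "for each significant prognostic variable".
- **3.4.2 Sample size.** The inputs are "To achieve a power of 80%, an alpha error rate of 0.05, a standard deviation of 5%, and an estimated effect size (W) of 0.20", and the result is that "a total of 198 participants will be required for our primary outcome". Allowing for 20% dropout, the target is 240. The threshold of 0.003 and any adjustment for multiplicity are absent, and the degrees of freedom are not given.

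**The concern.** No sentence says which threshold belongs to which test. Suppose a primary arm-by-time term gives p = 0.01. It fails the Bonferroni sentence and passes the closing one, so the plan does not settle the trial's main conclusion in advance.

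Each way of resolving this has a cost that the plan does not state. Under 0.003, the primary analysis runs at an alpha about 17 times smaller than the one used for sizing (0.05 / 0.003 = 16.7). Under 0.05, several primary measures are tested with no control of the overall error.

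The reporting sentence adds to the difficulty. A 95% interval can exclude an odds ratio of 1 while p exceeds 0.003, so the interval and the test can point in different directions.

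**Working it through.** **Inputs.** From 3.4.2: W = 0.20, alpha 0.05, power 80%, 198 evaluable, 240 enrolled, 20% dropout. From 3.8.1: thresholds 0.003 and 0.05. From the Abstract: three arms, 1:1:1. If exactly 20% of 240 drop out, 240 × 0.80 = 192 remain, so 192–198 is the relevant evaluable range.

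**Formula.** Power = P(noncentral chi-square with df and λ > critical value at alpha), with λ = N × W².

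**Step 1: reproduce 198.** At alpha 0.05 and 80% power, the required N is 197 with 1 df and 241 with 2 df. The stated 198 therefore matches a 1-df test. Three arms compared on a binary outcome would need 2 df.

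**Step 2: power at each threshold.**

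| df | N | λ = N × 0.04 | Power at 0.05 | Power at 0.003 |
|---|---|---|---|---|
| 1 | 198 | 7.92 | 80.4% | 43.9% |
| 1 | 192 | 7.68 | 79.1% | 42.2% |
| 2 | 198 | 7.92 | 71.3% | 33.4% |
| 2 | 192 | 7.68 | 69.9% | 31.8% |
| 1 | 240 (no dropout) | 9.60 | 87.3% | 55.2% |
| 2 | 240 (no dropout) | 9.60 | 79.8% | 43.9% |

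Reaching 80% at 0.003 would take 363 evaluable participants with 1 df or 424 with 2 df.

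**Step 3: if 0.05 governs instead.** Section 3.7.1 lists five primary measures: physical activity, diet, preventive medication, 10-year risk and lifetime risk. With independent tests, the chance of at least one false positive is 1 − 0.95⁵ = 22.6%. Positive correlation among the measures would lower this.

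**Limit of the check.** These are single-time chi-square figures, as in the plan's own calculation. The power of the GEE arm-by-time terms and of the interactions with risk perception cannot be computed from the document.

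**The case against.** The best defence is that a specific rule overrides a general one. The 0.003 sentence names the GEE models. The 0.05 sentence is a general closing line, and the same paragraph contains non-GEE tests that it could cover: the baseline chi-square, ANOVA and rank-sum comparisons and the attrition analysis. This is a reasonable reading, and for that reason the two sentences are better called unreconciled than flatly contradictory. A reader might infer that a primary p-value between 0.003 and 0.05 is both positive and negative under the plan; on the specific-over-general reading it is simply not significant. The defence does not rescue the sizing, however. It places the primary tests at 0.003, while 3.4.2 assumes "an alpha error rate of 0.05".

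Four other strong readings are tempting and are not supported.

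- **Power is 32%, without qualification.** That figure needs 2 df and 192 evaluable. On the basis that reproduces the plan's 198, it is 42–44%. With 2 df, part of the shortfall comes from the degrees of freedom and is already present at 0.05.
- **The correction covers 17 models, so family-wise error at 0.05 would be 58%.** The document never gives the divisor. Both 0.05 / 15 = 0.0033 and 0.05 / 18 = 0.0028 round to 0.003, and the count could be of models, parameters or contrasts. It is certain only that the threshold is applied to primary and secondary models alike.
- **Null results will be withheld.** The reporting sentence says how significant terms are presented. It does not say that other terms are omitted.
- **The powered variable is not the primary outcome.** The lifestyle variable in 3.4.2 names the same three behaviours as the first primary aspect in 3.7.1. How they would be combined is a separate question of endpoint definition.

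**Conclusion.** The point stands in this form: 3.8.1 states two thresholds with no rule dividing them, and 3.4.2 is sized at only one of them.

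If 0.003 governs the primary GEE tests, the 80% power is not delivered. At W = 0.20 and 192–198 evaluable, the like-for-like loss is from 79–80% to 42–44% with 1 df, or from 70–71% to 32–33% with 2 df. Even with no dropout, power at 0.003 is only 44–55%. If 0.05 governs, the five primary measures carry up to about 23% family-wise error, assuming independence.

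These figures rest on the plan's own W and a simple chi-square, with both df shown because the plan gives none. That the thresholds are unreconciled, and that the sizing alpha differs from the GEE alpha, depends on no calculation. This should be settled before any outcome is analysed by arm, because the primary conclusion could depend on the choice.

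**What to change.** 1. In 3.8.1, state which threshold governs the primary arm-by-time GEE tests. Confine the p < 0.05 sentence either to named non-GEE analyses, for example the baseline and attrition comparisons, or to one primary test named in advance.
2. State the number of tests behind 0.003 and what they are.
3. In 3.4.2, restate the power of the existing sample at the alpha and df actually used for the primary test. This does not require enrolling more participants.
4. Report every arm-by-time and arm-by-time-by-perception contrast, significant or not, with the interval level matched to the threshold (at 0.003, 100 × (1 − 0.003) = 99.7%).

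The thresholds can be reconciled without re-ranking the endpoints. If the single-primary-test option is taken with the lifestyle variable of 3.4.2, that variable needs a scoring rule, which neither 3.4.2 nor 3.7.1 gives. A 2-df test at 0.05 would still have only about 70–71% power on the plan's W.

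**Cost.** Wording only, but the stated power becomes less favourable.

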## Objective

2

This pilot study aims to clarify the optimal risk communication strategy by examining the compatibility between message framing (gain-framed, loss-framed, or no-framed) and risk perception subgroups (under-perceived vs. over-perceived vs. correct-perceived CVD risk), using a multi-center randomized controlled trial design in Zhejiang province, China. The specific objectives are as follows:

To evaluate the effect of message framing on CVD prevention behaviors among individuals with moderate and high CVD risk.To design a series of CVD risk communication messages based on message framing, then to implement the intervention program among individuals with different risk perception subgroups in the communities.To determine the optimal risk communication message for CVD risk populations with risk perception categories to achieve better CVD prevention behavior change, continuum maintenance, and risk reduction.

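### The final-model reporting rule ties odds ratios and confidence intervals to significance, so on its natural reading framing contrasts that miss the threshold get no estimate and those shown are selected for being large

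*Protocol article*

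**What the plan says.** Section 3.8.1 (Data analysis) fits GEE models with a logit link. Arm, time (T0, T1, T2), risk perception category and their interaction are the independent variables, and confounders are added for adjustment. Each parameter gets a Wald test. A Bonferroni correction is applied to all GEE models, "with a *p*-value threshold of less than 0.003 indicating statistically significant differences". The next sentence says the final model's results will be given as an odds ratio and 95% "confidence interval (*CI*) for each significant prognostic variable". Near its end the same section also sets general significance at p below "0.05 in two-sided tests".

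No other sentence promises an odds ratio or interval for an arm, arm-by-time or arm-by-perception term that is not significant. The section does promise descriptive statistics for all measurements.

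Section 2 (Objective) calls the study a pilot and lists among its aims: "To determine the optimal risk communication message for CVD risk populations with risk perception categories". Section 4 (Discussion) plans software that will match perception categories to messages on the strength of the results.

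**The concern.** Presenting results "for each significant prognostic variable" suits a model that searches for prognostic factors. Here the arm terms and their interactions are randomised contrasts, and they are the trial's answer whatever their p-value.

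If the sentence is followed as written, two things happen. A contrast that misses the threshold leaves a blank, and the reader cannot tell a small effect from an imprecise estimate. A contrast that passes has been picked because its estimate was large relative to its error, so it overstates the effect on average. Choosing a frame for each category requires comparing all frames in all categories, which a filtered table does not allow. Later work built on a pilot would inherit both the blanks and the inflated values.

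**Working it through.** **1. The plan's own figure.** Section 3.4.2 states "To achieve a power of 80%, an alpha error rate of 0.05, a standard deviation of 5%, and an estimated effect size (W) of 0.20", and that "a total of 198 participants will be required for our primary outcome". For a chi-square test with 1 df, N = (1.960 + 0.842)² / W² = 7.849 / 0.04 = 196.2, so 197. The next multiple of 3 is 198, or 66 per arm. The figure is reproduced with 1 df (2 df would give 241).

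**2. The same inputs at the GEE threshold.** √(198 × 0.04) = 2.814, and the critical value for p<0.003 is 2.968. Power = Φ(2.814 − 2.968) = 0.44, so even the design effect would be missed 56% of the time.

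**3. The contrast that the model estimates.** This is the difference between arms in change from T0 to T2 on the log-odds scale.

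- From section 3.4.2: T0 rate 30%; a 50% relative increase, taken as 30% to 45%; a 25% difference, read as 25 percentage points; 240 enrolled with 20% loss, so 240 × 0.8 / 3 = 64 per arm.
- Assumed, not in the documents: the no-frame arm stays at 30%; the 25-point effect is set against that arm (30% to 55%), although the protocol states it for gain versus loss; the within-person correlation is 0.5, either between the binary outcomes or on a latent normal scale (about 0.31 between the binary outcomes).
- True OR ratios: (0.45/0.55)/(0.30/0.70) = 1.91, log 0.647; (0.55/0.45)/(0.30/0.70) = 2.85, log 1.048.

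The variance per arm is [1/(p₀q₀) + 1/(p₂q₂) − 2ρ/√(p₀q₀p₂q₂)] / n. With ρ = 0.5 and n = 64:

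- control: (4.762 + 4.762 − 4.762)/64 = 0.0744
- framed arm: (4.762 + 4.040 − 4.386)/64 = 0.0690
- SE = √0.1434 = 0.379

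For 30% to 45%, z = 0.647/0.379 = 1.71. Power is Φ(1.71 − 1.96) = 0.40 at 0.05 and Φ(1.71 − 2.97) = 0.10 at 0.003, so about 60% and 90% are missed. With ρ = 0.31 the SE is 0.445, and about 69% and 93% are missed.

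Simulation with robust variance agrees. It gives these ranges over the two correlation scales:

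| Effect | True OR ratio | Missed, p<0.05 | Missed, p<0.003 | Median shown OR, p<0.05 | Median shown OR, p<0.003 |
|---|---|---|---|---|---|
| 30% to 45%, 64 per arm | 1.91 | 59–69% | 90–93% | 2.7–3.0 | 3.6–4.5 |
| 30% to 55%, 64 per arm | 2.85 | 20–34% | 57–73% | 3.2–3.5 | 3.9–4.8 |

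**4. Within one perception category.** If the categories were equal thirds, 64/3 gives about 21 per arm. The 25-point effect is then missed 63–72% of the time at p<0.05 and 92–95% at p<0.003.

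**5. A simpler check.** This compares two arms cross-sectionally at 66 per arm. At p<0.05, 30% vs 45% is missed 57% of the time, and a 25-point gap only 13–17%, depending on where it lies. At p<0.003 the figures are 88.5% and 46–53%. Among significant results the mean log OR is 1.5 times the truth (30% vs 45%) or 1.1 times (25 points) at 0.05, and 2.0 or 1.3 times at 0.003. Averaged over all results, it is 1.00 times the truth.

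**6. What a blank would hide.** Suppose 30% vs 45% were observed with 66 per arm. SE = √[1/(66 × 0.21) + 1/(66 × 0.2475)] = 0.365, so the OR is 1.91 with 95% CI exp(0.647 ± 1.96 × 0.365) = 0.93 to 3.91. That result is inconclusive, and under the stated rule it would not appear.

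**The case against.** The sentence never says that only significant variables will be shown. Its reference to prognostic variables could be loose wording for covariates, since confounders are mentioned a few lines before. Descriptive statistics are promised for everything, so arm-level results would not vanish, and the layout of result tables is often left to an analysis plan. These points soften the reading but do not remove it. The sentence is a stated rule about the final model's results, not an omission. It makes no exception for the randomised terms, and descriptive statistics are not adjusted contrasts with intervals.

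The objection to the size has more force. The miss rates depend on an undocumented correlation and its scale, on a control arm that stays at 30% although it receives the same content and incentives, and on equal perception categories. Low power and the unresolved pair of thresholds cause much of the loss, and a reporting change cures neither. The figures are therefore ranges that illustrate the filter's effect.

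A reader might also infer that the plan will declare frames alike when a contrast is not significant, or will drop randomised terms from the model. The documents say neither. Nor do they support a claim that every contrast is missed well over 20% of the time: at p<0.05 the 25-point contrast is missed 20% under one assumption here and 13–17% cross-sectionally.

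**Conclusion.** The point stands as a flaw in a stated reporting rule. On its natural reading, section 3.8.1 filters the randomised contrasts by significance, which works against the aim of choosing a frame for each category. This holds whichever of the two thresholds governs, because selection by significance inflates what is shown whenever power is below 100%.

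The size varies. Inflation is modest for the overall 25-point contrast at p<0.05 (median 3.2–3.5 against 2.85). It is large for the 15-point effect at p<0.003 (3.6–4.5 against 1.91). Most real effects would be missed within a single perception category, if the categories are equal thirds. All of this rests on the assumptions listed in the working. The case for changing the sentence does not depend on any one figure. The flaw affects reporting; the sample size, the model and the error rate are not in question on this point.

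**What to change.** Replace the sentence in section 3.8.1 with:

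> *ORs and 95% CIs will be presented for every prespecified arm-by-time contrast (gain vs no frame, loss vs no frame, gain vs loss, at T1 and T2), overall and within each perception category, whether or not significant, and no randomised term will be removed from the final model for non-significance.*

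The last clause is a safeguard, since the protocol does not say that such terms will be removed. A similarity margin is not needed, because the protocol plans no claim that frames are equivalent.

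The cost is a longer results table, in which some contrasts will have wide intervals and read as inconclusive. No participants, data, models or error rates change.
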